### Interventions

Subjects will receive varenicline for 12 weeks, using standard dosing: 0.5 mg once daily for 3 days, then 0.5 mg twice daily for 4 days, followed by 1 mg twice daily for 11 weeks. Subjects will be randomly assigned to receive varenicline via: 1) treatment as usual (TAU) or 2) modified directly observed therapy (mDOT). Most subjects will have public insurance that should cover the cost of varenicline; for those who do not, varenicline will be purchased from a local pharmacy using research funds.

### DOT Intervention

Subjects in the mDOT arm will receive: 1) directly observed varenicline doses at the same time as they receive a methadone dose at their methadone program, between 3 and 6 times per week; and 2) take-home doses packaged in individual pill boxes for self-administration on days off and evenings (Figure 1). In addition, methadone clinic nurses will assess side effects using a standard script and will refer subjects to on-site medical providers for treatment if side effects are reported.

**Figure 1 F1:**
[figure not shown]
**Example mDOT varenicline pill trays. A**. Methadone clinic visits 3 days per week. **B**. Methadone clinic visits 6 days per week. This figure illustrates mDOT varenicline pill box labels indicating observed and take-home varenicline doses, according to subjects’ methadone clinic schedule.

We describe the intervention as ‘modified directly observed therapy’ because varenicline ingestion will be observed at the methadone window 3–6 days per week based on the subject’s methadone clinic schedule. Furthermore, varenicline is a twice-daily medication, and only one of two daily varenicline doses can be observed. For example, if a subject receives methadone at his/her program Monday through Saturday and a take-home dose of methadone on Sunday, s/he would receive observed varenicline at the same time s/he receives methadone Monday through Saturday (for a total of six observed doses), and would get pill boxes for evening and Sunday varenicline doses (eight unobserved doses weekly). Subjects will be instructed to return the pill boxes for unobserved doses at their next clinic visit, whether or not they have taken the pills.

To minimize nursing burden, trays of pill boxes will be prepared by research assistants, indicating varenicline dosing and dates of administration, and color-coded labels will indicate whether the dose is directly observed or self-administered (for days off and evenings). Each tray will hold seven removable pill boxes, with compartments for morning and evening varenicline doses. The study physician will call in varenicline prescriptions to a single, designated, community pharmacy that delivers medications to the DoSA central pharmacy. Empty, labeled trays also will be delivered to the central DoSA pharmacist, who will fill pill boxes with varenicline for each subject. Filled trays will be delivered from the central pharmacy to the methadone clinics every 2 weeks, along with scheduled methadone deliveries.

### TAU Control condition

Subjects in the TAU arm will pick up prescribed varenicline from a local pharmacy of their choosing and self-administer all varenicline doses (once daily for 3 days, then twice daily).

### Counseling and medication education

All subjects in both groups will receive a single session of brief, physician, smoking cessation counseling based on the Public Health Service 5As framework (ask, assess, advise, assist, arrange follow-up) [31]. Brief advice has been shown to increase the likelihood of successful smoking cessation [31], is associated with outcomes comparable to tailored motivational counseling among methadone-maintained smokers [8], and is easily implemented in complex clinical settings. Subjects also will receive a brochure promoting medication adherence, as well as verbal and written instructions on varenicline administration and management of anticipated side effects. If subjects report persistent or severe treatment-emergent symptoms over the intervention period, they will meet with the study physician for assessment and brief counseling on symptom management.

### Randomization

Subjects will be randomized a 1:1 ratio in variable size blocks of 2–8 via central, computer-generated randomization. Randomization will be stratified by clinical site and HIV status. We will randomize in blocks to ensure comparison groups of approximately equal size. To ensure concealment of allocation, a centrally-located data manager will generate the allocation sequence and store the sequence in a password-protected file. After the study physician confirms a subject’s eligibility, she will call the data manager, who will assign the subject to a treatment group. Since the intervention is not blinded, we will vary block size to prevent anticipation of treatment arm assignment.

### Visit schedule and measures

Research visits will be scheduled at baseline and at weeks 1, 2, 3, 6, 9, 12, and 24 (Table 1). We will collect survey data using Audio Computer-Assisted Self-Interview (ACASI), which has been shown to improve reporting of stigmatized behaviors. Subjects will be reimbursed up to $110 for completing all research assessments. Retention will be enhanced by flagging subjects for research visits at the methadone clinic reception desk, tracking contact information of subjects and their close contacts at each study visit, reimbursement for completion of assessments, and on-site data collection at subjects’ clinics.

**Table 1 T1:** Timing of study measures

	**Baseline/Start Rx**						**End of treatment**	
**Week**		1	2	3	6	9	12	24
**Study measures**								
Sociodemographic characteristics	X							
Tobacco use behavior, FTND^a^	X			X	X	X	X	X
Smoking endpoints^b^				X	X	X	X	X
Medication adherence		X	X	X	X	X	X	
Mini-International Neuropsych. Interview	X			X	X	X	X	X
Modified scale for suicidal ideation	X			X	X	X	X	
Brief symptom Inventory	X			X	X	X	X	X
Medication adverse events		X	X	X	X	X	X	
Alcohol and other drug use	X			X	X	X	X	X
Urine toxicology tests	X			X	X		X	
Medication adverse events		X	X	X	X	X	X	
**Subject reimbursement**								
$ Amount^c^	$15	$10	$10	$15	$15	$15	$15	$15

^a^Fagerström Test for Nicotine Dependence.

^b^Carbon monoxide-verified abstinence, number of cigarettes smoked per day, Fagerström Test for Nicotine Dependence score, quit attempts lasting ≥ 24 hours.

^c^To ensure pill count completion, TAU subjects will be given partial reimbursement ($5-$10 dollars per visit) for research assessments and $5 for completion of pill counts at each follow-up visit during the intervention period.

### Adherence measures

Our primary outcome is adherence (as a continuous measure) by pill count. Pill counts are an objective measure that have been shown to correlate with electronic monitors [32]. The amount of medication taken during the 12-week treatment course will be expressed as a percentage of the target dose. These are established measures used in other DOT trials in our setting [29,33]. Self-report is the most practical adherence measure for clinical use, and it has been shown to correlate with clinically relevant outcomes in several studies [34-37]. Though self-report is subject to recall and reporting bias and may overestimate adherence [32,36,38,39], we will use self-report as a second measure of adherence because it is easy to administer and is generalizable. Because electronic monitors (using medication event monitoring systems [MEMs]) cannot be used in the mDOT arm, we have chosen not to use MEMs.

### Tobacco use measures

Our primary tobacco use outcome is biochemically validated 7-day point prevalence abstinence at each follow-up visit, with abstinence defined as including both self-reported smoking abstinence and carbon monoxide (CO) < 8 p.p.m. (Micro Smokerlyzer®, Bedfont Scientific) [40]. Self-reported tobacco abstinence will be measured at all visits by asking participants, “Have you smoked at least part of a cigarette in the past 7 days, even a puff?” Our secondary tobacco outcome measures include: 1) number of cigarettes smoked per day; 2) Fagerström Test for Nicotine Dependence score; 3) quit attempts lasting ≥ 24 hours; and 4) durability, measured by CO-verified tobacco abstinence at week 24.

### Potential moderating variables: psychologic symptoms

We will assess incident psychologic symptoms at weeks 3, 6, 9, and 12 using: 1) M.I.N.I. [41], which is a short, structured, diagnostic interview for DSM-IV Axis I disorders; 2) the Columbia Suicide Severity Rating Scale, a structured interview that assesses suicidal ideation, plans, intent, and behavior [42]; and 3) the Brief Symptom Inventory (BSI [43]), a measure of general psychological symptom status that can be monitored over time.

### Potential moderating variables: Alcohol and drug use

We will assess alcohol and drug use at baseline and at weeks 3, 6, 9, and 12 via: 1) the Addiction Severity Index, Lite version [44]; 2) the Alcohol Use Disorders Identification Test [45]; and 3) urine toxicology tests.

### Medication adverse effects

Adverse events will be evaluated at each follow-up visit during the intervention period, using both a structured questionnaire that assesses the presence of specific symptoms that have been reported among varenicline subjects in published clinical trials, and an open-ended review of treatment-emergent symptoms, defined as symptoms that emerged or increased in intensity following the start of study medication.

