#### Addressing varenicline risk potential

Case reports of behavior change, agitation, depression, and suicidality among patients taking varenicline led to an FDA boxed warning in 2009 [47]. Despite a growing body of research demonstrating the safety of varenicline among patients with mental illness and substance use disorders [48-56], we will take multiple precautions to address varenicline’s psychiatric risk potential.

Prior to enrollment, information regarding potential psychiatric risks will be discussed with subjects during the informed consent process. During screening, a physician will assess potential subjects for current psychiatric illness or suicidal ideation using structured instruments. Individuals with psychiatric symptoms not receiving psychiatric care will be referred to a mental health center.

Subjects will be assessed for incident psychiatric symptoms throughout the intervention period. At brief visits (weeks 1 and 2), and weeks 3, 6, 9 and 12, the interviewer will ask open-ended questions about symptoms that have emerged or increased in intensity since the prior visit. At week 3, 6, 9, and 12 follow-up visits, psychiatric symptoms will be assessed via structured instruments. Prior to concluding the research visit, the research assistant will review flags programmed into the computerized survey record for symptoms consistent with incident major depressive or manic episode, psychotic disorder, or suicidal ideation and will refer subjects to outpatient or emergency treatment according to detailed study protocols.

If subjects meet criteria for current major depressive or manic episode, psychotic disorder, or suicidal ideation with plan or intent, varenicline will be discontinued. To facilitate medication discontinuation among TAU group subjects who fill varenicline prescriptions at community pharmacies of their choosing, prescriptions will not be given directly to study subjects; rather, the study physician will call in all prescriptions and track the pharmacies used. If DOT group subjects meet criteria for medication discontinuation, the study physician will notify the study pharmacy and the methadone clinic nurses.

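### The structured adverse-event checklist has no pre-dose administration, so its own data cannot separate pre-existing from treatment-emergent symptoms (minor, cheap to improve)

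*Protocol article*

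**What the plan says.** The section on medication adverse effects sets the timing: "Adverse events will be evaluated at each follow-up visit during the intervention period". It names two instruments.

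- **Checklist:** "a structured questionnaire that assesses the presence of specific symptoms", the symptoms being those reported in published varenicline trials.
- **Open-ended review:** this covers treatment-emergent symptoms, "defined as symptoms that emerged or increased in intensity following the start of study medication".

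In Table 1 the row "Medication adverse events" is printed twice with identical marks, at weeks 1, 2, 3, 6, 9 and 12. The baseline column, headed "Baseline/Start Rx", is blank in both. The M.I.N.I., the suicidal-ideation scale and the Brief Symptom Inventory (BSI) do have a baseline mark in the same table.

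The section on addressing varenicline's risk potential says how the open-ended part is put to participants at those same six visits: "the interviewer will ask open-ended questions about symptoms that have emerged or increased in intensity since the prior visit".

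**The concern.** A checklist that records whether a symptom is present, and is first given after a week of treatment, has no reference point of its own. A participant who already had nausea or insomnia before the first dose answers at week 1 exactly as does one in whom it is new. (These two symptoms are examples; the article does not list the items.) Without a pre-dose rating, worsening cannot be read from the checklist either.

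Usually an untreated arm would show how much of the reported frequency is background. Here every participant receives varenicline, so each participant's own pre-dose answer is the natural reference. What is at stake is the interpretation of symptom frequencies from this one instrument. A pre-dose record cannot be recovered once dosing has begun.

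**Working it through.** The article states no figure on this point, so the check is of the schedule against the text.

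**Step 1. Count the scheduled assessments (Table 1).**

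| Measure | Baseline | On treatment | Week 24 |
|---|---|---|---|
| Adverse events (checklist and open-ended review) | 0 | 6 (weeks 1, 2, 3, 6, 9, 12) | 0 |
| M.I.N.I. | 1 | 4 (weeks 3, 6, 9, 12) | 1 |
| BSI | 1 | 4 (weeks 3, 6, 9, 12) | 1 |
| Suicidal-ideation scale | 1 | 4 (weeks 3, 6, 9, 12) | 0 |

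Text and table agree that adverse-event recording is confined to on-treatment visits. This is a stated schedule, not a detail left unsaid.

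**Step 2. Ask what each instrument needs.**

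- The open-ended review asks the participant about onset or worsening. The comparison with the earlier state is made by recall, so no baseline form is needed.
- The checklist, as described, asks about presence. Sorting a positive answer into pre-existing or new requires the same item before dosing, and none is scheduled.

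**Step 3. See whether other baseline records fill the gap.** The M.I.N.I., suicidal-ideation scale and BSI give a pre-dose reference for psychiatric diagnoses, suicidality and general psychological distress. The section on participants adds a physician's clinical interview and physical examination before eligibility is confirmed. None of these is said to record the checklist's symptoms item by item. What remains uncovered is therefore mainly somatic.

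**Step 4. See whether a comparison group fills the gap.** Both arms take varenicline for 12 weeks. A contrast between arms informs on the mode of delivery, not on the background rate of symptoms.

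**Step 5. Illustrate the possible size.** Let *b* be the share with a listed symptom before dosing, all persisting, and let 10% of the others develop it on treatment. Both rates are assumptions; the article gives neither.

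- Share reporting the symptom present = *b* + (1 − *b*) × 0.10
- Share with a newly emergent symptom = (1 − *b*) × 0.10

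| Assumed *b* | Present | Newly emergent |
|---|---|---|
| 0.20 | 0.20 + 0.80 × 0.10 = 28% | 0.80 × 0.10 = 8% |
| 0.40 | 0.40 + 0.60 × 0.10 = 46% | 0.60 × 0.10 = 6% |

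In this illustration, a higher background raises the checklist frequency while the newly emergent share falls.

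**The case against.** The strongest reply is that little in the trial depends on this. It compares two ways of delivering the same drug, and its outcomes are adherence and abstinence. Randomization is expected to balance background symptoms between the arms, and estimating varenicline's absolute side-effect rate is not a stated aim. The article is also condensed, so the full protocol may describe grading or attribution rules for the checklist. All of this stands and keeps the point minor. It does not remove the point, because the article is explicit about timing, and no later rule can supply a missing pre-dose answer.

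A reader might infer more than the document supports:

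- **That the treatment-emergent definition is unusable.** It is attached to the open-ended review, which asks about new or worse symptoms directly and so can also pick up worsening of an existing symptom.
- **That there is no baseline symptom record at all.** Psychiatric and psychological measures are taken at baseline, and a clinical interview and examination come before treatment.
- **That pre-existing symptoms will be counted as varenicline events.** No section says that a positive checklist item is attributed to the drug. The supported statement is that the checklist cannot tell the two apart.
- **That contaminated rates go to the Data Safety and Monitoring Committee.** The section on confidentiality and research protections lists trial progress, incident psychiatric illness, serious or unanticipated adverse events, pregnancies and protocol deviations. Checklist rates are not listed.
- **That the two descriptions of the open-ended review conflict.** One counts from the start of medication; the other asks about "symptoms that have emerged or increased in intensity since the prior visit". Because the baseline visit is labelled as the start of treatment, the week 1 question reaches back to that start, and later visits extend the window. Successive windows add up to the definition. A symptom captured at week 1 is not lost because it persists.

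**Conclusion.** The point holds in a limited form. The structured checklist has no baseline administration, its answers are described as presence of symptoms, and no arm is untreated. Checklist answers, mainly for somatic symptoms, therefore cannot be divided into pre-existing and treatment-emergent from the checklist's own data. The open-ended review and the efficacy outcomes are unaffected.

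This rests on two readings of the article: that the checklist asks about presence without asking about onset, and that the baseline instruments do not cover its items. If the full protocol's form asks about onset, the problem is reduced to reliance on recall. The size is unknown, and the percentages under the working are illustrations, not estimates for this trial. I class it as a minor, cheap improvement.

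**What to change.** Give the same checklist, with an intensity rating, at the existing baseline visit before the first dose, and add an X in the Baseline column of the adverse-event row in Table 1. Use the same intensity rating at the on-treatment visits. Class a checklist symptom as treatment-emergent only if it was absent, or rated less intense, at baseline. For participants already enrolled without a baseline form, report checklist answers as prevalence and do not label them treatment-emergent.

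The cost is a few extra minutes of questionnaire time at a visit that already takes place, plus one line in an amendment.

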### Major hypotheses and analytic plans

We will review and summarize data using descriptive summaries and graphical analyses to ensure recorded values are within appropriate ranges and to check for outliers and abnormal values. Interim analyses will not guide recruitment decisions.

### Varenicline adherence

We hypothesize that adherence in the mDOT arm will be higher than in the TAU arm throughout the intervention period. We will apply a mixed effects linear model to test the significance of the mDOT effect on the repeatedly measured pill count adherence outcome at weeks 1, 2, 3, 6, 9, and 12. This model accounts for within-subject longitudinal outcome correlation by taking the subject-level intercept as random, and it is robust in the context of missing data. The model will also include variables not equally distributed between the study arms at baseline, as well as psychiatric symptoms and substance abuse. All analyses will use an intent-to-treat approach.

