### Moderating effects of drug use and psychiatric symptoms

We hypothesize that ongoing drug use and psychiatric symptoms will negatively moderate adherence effects. The dependent variable will be varenicline adherence. Potential moderating variables include cocaine, heroin, benzodiazepine, or marijuana use (defined as a binary variable based on either self-reported use or positive urine toxicology result); hazardous alcohol use (defined as AUDIT score ≥ 8 for men and ≥ 4 for women); incident major depressive, manic, or psychotic episodes; suicidal ideation with plan or intent; and symptoms of psychologic distress (BSI Global Severity Index T score ≥ 63). We will test moderators using a treatment group x moderating variable interaction term, and set an alpha significance level of 0.15 for interaction analyses.

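### The primary adherence model selects covariates by observed baseline imbalance and adds psychiatric and substance-use variables without fixing when they are measured

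*Protocol article*

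**What the plan says.** Under Adherence measures the article fixes the outcome: "Our primary outcome is adherence (as a continuous measure) by pill count". Under Varenicline adherence it fixes the model: "We will apply a mixed effects linear model to test the significance of the mDOT effect on the repeatedly measured pill count adherence outcome". The model has a random subject intercept, and the outcome visits are weeks 1, 2, 3, 6, 9 and 12. It then sets the covariates: "The model will also include variables not equally distributed between the study arms at baseline, as well as psychiatric symptoms and substance abuse". The same paragraph says that all analyses follow intent-to-treat.

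Four other places bear on that sentence:

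- Randomization: "Randomization will be stratified by clinical site and HIV status". The covariate sentence names neither factor.
- Potential moderating variables, psychologic symptoms: "We will assess incident psychologic symptoms at weeks 3, 6, 9, and 12".
- Potential moderating variables, alcohol and drug use: "We will assess alcohol and drug use at baseline and at weeks 3, 6, 9, and 12 via" three instruments.
- Moderating effects: the psychiatric moderators include "incident major depressive, manic, or psychotic episodes", and the hypothesis concerns drug use that is ongoing.

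Table 1 marks the M.I.N.I., the Brief Symptom Inventory (BSI), and alcohol and drug use at baseline as well as at follow-up.

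**The concern.** There are two separate problems in one sentence.

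First, the imbalance rule. Randomisation makes any baseline difference a chance event, and its size says nothing about whether the variable predicts adherence. Under this rule the primary model is unknown until the arms have been compared, and two analysts with different candidate lists or thresholds would fit different models. Strong predictors that happen to be balanced are left out. Site and HIV status are roughly balanced by design, so the rule tends to pass over the very factors used in the randomisation.

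Second, timing. The wording joins psychiatric symptoms and substance abuse to the baseline variables as a separate group and gives no visit. If these are follow-up values, the model conditions on variables that the arm may change. At stake is whether the primary estimate is the intent-to-treat effect that the plan claims.

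**Working it through.** The plan gives no figure on this point to reproduce. Its adherence sample size is used only to find a plausible SD.

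**Context: SD.** The sample size section gives 57% against 44%, two-sided alpha 0.05, and 11, 14 and 17 per group at ICC 0.1, 0.2 and 0.3. SD, power and number of measurements are not stated. Assuming 80% power, SD 0.20 and m = 5 measurements:

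- n0 = 2 × [0.20 × (1.960 + 0.842) / 0.13]² = 37.2
- n = n0 × [1 + (m − 1) × ICC] / m = 10.4, 13.4 and 16.4, which round up to 11, 14 and 17.

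An SD of about 20 points is therefore consistent with the plan, but not confirmed by it.

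**Step 1: how often the rule acts by chance.** Assume K independent baseline variables, each judged at threshold s. Then P(at least one enters) = 1 − (1 − s)^K. The documents give neither K nor s, so a range is shown.

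| K | s | P(at least one) |
|---|---|---|
| 10 | 0.05 | 1 − 0.95^10 = 0.40 |
| 10 | 0.10 | 1 − 0.90^10 = 0.65 |
| 15 | 0.05 | 1 − 0.95^15 = 0.54 |
| 20 | 0.05 | 1 − 0.95^20 = 0.64 |

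This shows how unfixed the model is. It does not measure harm.

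**Step 2: effect on the test.** Simulation under no treatment effect: 50 per arm, one adherence value per subject, 10 independent covariates that together explain 20% or 40% of outcome variance, 10,000 runs per setting, nominal alpha 0.05.

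| Variance explained | Threshold | Unadjusted | Selected by imbalance | All 10 prespecified |
|---|---|---|---|---|
| 20% | 0.05 | 0.0452 | 0.0402 | 0.0481 |
| 20% | 0.10 | 0.0500 | 0.0437 | 0.0540 |
| 20% | 0.20 | 0.0503 | 0.0411 | 0.0462 |
| 40% | 0.05 | 0.0456 | 0.0379 | 0.0500 |
| 40% | 0.10 | 0.0524 | 0.0329 | 0.0479 |
| 40% | 0.20 | 0.0493 | 0.0305 | 0.0496 |

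The Monte Carlo standard error is about √(0.05 × 0.95 / 10,000) = 0.002. Selection by imbalance is below nominal in every row. When a prognostic variable is balanced and therefore left out, its variance stays in the residual and the standard error is too large for that sample.

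**Step 3: which visit the psychiatric and substance-use values come from.**

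- Pointing to follow-up: these variables are listed apart from the baseline variables; the moderator sections call the psychiatric ones incident and the drug use ongoing; and the eligibility criteria exclude current major depressive, manic and psychotic states, so those episodes have essentially no baseline variation.
- Pointing to baseline: Table 1 and the alcohol and drug use section include baseline assessments.
- Visit mismatch: adherence is modelled at weeks 1 and 2, but Table 1 has no M.I.N.I., BSI or drug-use assessment then. Concurrent follow-up values would be missing for two of the six outcome visits.

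The text does not settle the question.

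**Step 4: what follow-up values would do.** Simulation with a true effect of 13 points, SD 20, 50 per arm, 3,000 runs, and a binary covariate present in about half of controls. The arm shifts it by 0, 0.25 or 0.5 on a probit scale. A cause that explains 30% of outcome variance also drives the covariate with strength 0, 0.5 or 1.

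| Arm affects covariate | Shared cause | Adjusted estimate | Unadjusted |
|---|---|---|---|
| no | none to strong | 12.91 to 12.99 | 12.91 to 12.98 |
| yes | none | 12.96, 13.01 | 12.97, 12.99 |
| 0.25 | 0.5 / 1 | 12.24 / 12.19 | 12.92 / 13.04 |
| 0.5 | 0.5 / 1 | 11.71 / 11.31 | 13.08 / 13.03 |

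The estimate moves only when both conditions hold. With the opposite sign for the arm's effect on the covariate, it would move up. A covariate on the pathway from arm to adherence was not simulated. Such a pathway is possible: the safety section has varenicline discontinued when specified psychiatric criteria are met, so an episode can directly reduce pills taken. Adjusting for it would then remove part of the total effect.

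**The case against.** The strongest reply has four parts.

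- **Timing.** A reader might infer that the plan adjusts for post-randomisation variables. The covariate sentence does not say so, baseline values of the same measures are collected, and the words incident and ongoing come from the moderator sections. This stands: what can be shown is that the timing is not fixed and that a follow-up reading is plausible.
- **Strata.** A reader might infer that site and HIV status are excluded. They are only unnamed. The wording is additive, and a condensed article may leave stratification covariates to the full analysis plan. Leaving strata out of a linear model costs efficiency and does not bias the effect. This also stands. The strata matter here only because the stated imbalance rule tends to pass over balanced factors.
- **False positives.** A reader might infer that data-driven selection inflates type I error. The simulation shows the opposite.
- **Consequence.** This is described as a pilot. The plan puts the adherence requirement at 11 to 17 per group, while about 50 × 0.75 = 37.5 per arm would remain after attrition. On those figures a modest loss of precision matters little.

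None of this removes the imbalance rule. It is stated outright for the primary outcome, so it is not a detail left to an unseen analysis plan.

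**Conclusion.** The point holds in two parts of different strength.

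The imbalance rule is a definite defect of prespecification. Its cost is an unfixed model and a somewhat conservative test: 0.030 to 0.044 against a nominal 0.05, assuming 10 independent covariates that explain 20% to 40% of outcome variance. It is not a source of bias or of excess false positives.

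The timing of the psychiatric and substance-use covariates is a definite ambiguity with a conditional consequence. If follow-up values are used, the intent-to-treat effect may be lost. In the illustration the shift was roughly 0.7 to 1.7 points out of 13 (12.92 − 12.24 = 0.68; 13.03 − 11.31 = 1.72), on assumed inputs. There is no shift if the arm leaves these variables unchanged. If the arm does affect them, bias arises when they share a cause with adherence or lie on the pathway to it.

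It should be corrected before the arms are compared, but it does not undermine the trial's ability to answer its primary question.

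**What to change.** Replace the covariate sentence with a fixed specification:

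- Delete selection by observed baseline imbalance.
- Prespecify the covariates: clinical site, HIV status, baseline BSI and baseline drug use.
- State that psychiatric and substance-use covariates in this model are baseline values only.
- Keep follow-up values of these variables for the moderator or secondary analyses.

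An arm-by-visit term, scheduled clinic days per week, or the Fagerström score in the abstinence model are optional choices and not part of this defect.

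The cost is wording and a few degrees of freedom: 2 for three sites, plus 1 each for HIV status, a single BSI score and a single binary drug-use indicator, 5 in all. The BSI and drug-use baselines are in Table 1, and site and HIV status must be known to randomise, so no new data are needed.
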